#### Adverse events

Participants will be encouraged to report any untoward health/medical related events (i.e. adverse events) regardless of likely cause. This will include possible adverse reactions (e.g. increase in heel pain, onset of new pain or injury elsewhere) that they experience during the study to a study investigator (RM) and/or their physiotherapist. If an adverse event is associated with the foot exercise plus education intervention, the physiotherapist will modify the exercise prescription and/or load management advice accordingly until a reduction in symptoms is reported. In the event of a sustained increase in heel pain or aggravation of another area of pain, standard clinical practice principles will apply and provision of any treatments outside of the study protocol (e.g. taping) will be recorded in the physiotherapist’s treatment notes and reported to a study investigator (RM). If symptoms associated with the adverse event are unable to be resolved, the intervention will be ceased and the participant encouraged to remain in the trial to enable follow-up data collection.

### Outcome measures

To ensure sufficient information is obtained to inform the design of a full-scale RCT, a comprehensive set of primary and secondary outcome measures will be recorded (Table 2). Outcome measures will be assessed at baseline and 12-week time-points (at the end of the intervention period). The 12-week time period for measuring outcomes allows an adequate timeframe to observe adaptations, allowing for (a) a 2-week lead in period of familiarisation and movement competency training, (b) an 8-week strengthening programme, (c) graduated progression of exercise, and (d) integration into functional tasks. All outcome measures will be obtained by an assessor who is blinded to group allocation ([name]).

**Table 2 Tab2:** Outcome measurements

		STUDY PERIOD		
		Enrolment/ Baseline	Post-allocation	Close-out
**TIMEPOINT**^**a**^		**t**_**0**_	**t**_**1**_	**t**_**2**_
**ENROLMENT:**				
Eligibility screen		X		
Informed consent		X		
Allocation		X		
**INTERVENTIONS:**				
Foot exercise and education				
Brief advice				
**ASSESSMENTS:**				
Participant characteristics		X		
**Primary outcome measures**				
*Feasibility*				
Number of eligible participants				X
Willingness to enrol				X
Recruitment rate				X
Adherence				X
Logbook completion				X
Adverse effects				X
Dropout rates				X
*Credibility*				
Borkovec and Nau Questionnaire		X	X	
*Acceptability*				
Number of sessions attended				X
Adherence to foot exercises				X
Additional treatment sought				X
Early withdrawal				X
**Secondary outcome measures**				
*Patient reported outcomes*				
First step pain in previous week		X	X	
Worst pain in previous week		X	X	
Average pain in previous week		X	X	
Foot and Ankle Ability Measure		X	X	
Foot Health Status Questionnaire		X	X	
Global Rating of Change Score			X	
Pain Self-Efficacy Scale		X	X	
Active Australia Survey		X	X	
*Physical measurements*				
Intrinsic foot muscle morphology (MRI & ultrasound)		X	X	
Plantar fascia thickness (ultrasound)		X	X	
Intrinsic foot muscle motor performance		X	X	
Foot Posture Index		X	X	
Foot mobility		X	X	
Ankle dorsiflexion range of motion (standing lunge test)		X	X	
Toe flexor strength (dynamometry)		X	X	
Plantar flexor strength (standing heel rise test)		X	X	

^**a**^t_0_ = Baseline, t_1_ = week 12, t_3_ = end of data collection all participants

#### Primary outcome measures

Primary outcomes of this trial will determine the feasibility of conducting a full-scale RCT, as well as the credibility and acceptability of the 12-week foot exercise and education intervention in the treatment of PHP.

*Feasibility* will be assessed by: (i) the number of eligible participants (number of eligible participants to number of volunteer responses to trial advertisements); (ii) willingness of volunteers to enrol (number of eligible volunteers to number of enrolled participants); (iii) recruitment rate (number of enrolled participants to the duration of the recruitment period, expressed as participants per week); (iv) adherence with allocated intervention (percentage of physiotherapy visits completed by the participant with respect to the total sessions scheduled; percentage of home training sessions completed by the exercise group with respect to the total training sessions scheduled); (v) log book completion (percentage of training sessions recorded by the participant with respect to the total training sessions to be recorded); (vi) drop-out rate (number of participants who withdrew from the study); and (vii) adverse events.

2.*Credibility* of treatment will be evaluated using the Borkovec and Nau questionnaire [25] which consists of six items related to patient expectations of the allocated treatment (i.e. how much the participant believes that the therapy they are receiving will help to reduce their heel pain). The questionnaire has good test-retest reliability with intra-class correlation coefficients (ICCs) of 0.82 for expectancy and 0.75 for credibility [25]. It will be completed by participants immediately following the first treatment session and at 12-week follow-up.

3.*Acceptability* of the foot exercise intervention and the brief advice intervention will be assessed by: (i) the number of sessions attended as a percentage of the total number of sessions scheduled; (ii) adherence to the foot exercise intervention (percentage of physiotherapy visits completed by the participant with respect to the total sessions scheduled; percentage of home training sessions completed by the participant with respect to the total training sessions scheduled); (iii) additional treatments sought; and (iv) reasons for early withdrawal.

To further explore aspects of feasibility, credibility and acceptability, one-on-one semi-structured interviews will be conducted by the chief investigator. Interviews with participants will be conducted at the conclusion of the 12-week intervention period after completion of follow-up measures and with trial physiotherapists at the conclusion of data collection for all participants. Additional file 8 outlines the question guides.

#### Secondary outcome measures

In the absence of a defined core outcome set for PHP, we will record a comprehensive set of measures that are likely to capture all health related domains of PHP. For example, we will record record a numeric rating scale for first step pain, worst pain and average pain to ensure we are covering the pain aspect of PHP. We will use the Foot and Ankle Ability Measure to capture the disability; the Foot Health Status Questionnaire to evaluate quality of life; the Pain Self-Efficacy Questionnaire to get a sense of the psychological aspects; the Active Australia Survey to gauge how active the participants are; and we will capture foot muscle morphology, foot posture index, foot mobility, toe flexion strength, ankle dorsiflexion, and ankle plantarflexor strength to gain a representation of structural and functional aspects of PHP. These feasibility/practicality of use, response profile (effect size), and completion rates will be used to guide decisions in future trials. For participants with bilateral pain, the foot that the participant reports as having the worst symptoms will be evaluated.

Patient-reported outcome measures will be used to evaluate pain, physical function, physical activity level and pain self-efficacy.

*Pain severity:* An 11-point numerical rating scale anchored by 0 (no pain at all) and 10 (worst pain imaginable) will be used to rate first step, worst and average level of pain that the participant has experienced in the past week [26]. The numerical rating scale is reported to be more responsive, easier to administer and preferred by patients compared to other pain scales [27]. A 2-point change is reported to be a clinically important difference in individuals with chronic pain [26].

2.*Physical function:* Physical function will be evaluated using the Foot and Ankle Ability Measure and the Foot Health Status Questionnaire. The Foot and Ankle Ability Measure consists of a 21-item activities of daily living subscale and an 8-item sports subscale. Each item is rated by the patient on a 5-point scale as ‘no difficulty’ through to ‘unable to do’. Individual item scores (‘no difficulty’ = 4 through to ‘unable to do’ = 0) are summed and expressed as a percentage of the total score for each subscale (activities of daily living = 84, sports subscale = 32) where 100 represents full function. The Foot and Ankle Ability Measure is a reliable, responsive, and valid measure of physical function for individuals with a broad range of musculoskeletal disorders of the lower leg, foot, and ankle [28]. The minimal clinically important difference is reported as 8 and 9 points for the activities of daily living and sports subscale, respectively [28]. The Foot Health Status Questionnaire consists of 13 items arranged in 3 subscales (foot pain, foot function and general foot health) and converted to a score where 0 represents poor foot health and 100 optimal foot health [29]. The minimal important difference is reported as 14, 7 and 9 points for the foot pain, foot function and general foot health subscales, respectively [30].

3.*Pain self-efficacy:* The Pain Self-Efficacy Questionnaire consists of 10 items, and will be used to assess the confidence participants have in performing activities while in pain [31]. Pain self-efficacy is associated with key outcomes related to chronic pain and to have implications for subsequent functioning [32]. Previous research has reported high test-retest reliability (Pearson’s r = 0.73) [31].

4.*Global rating of change:* Global rating of change score will be obtained using an 11-point scale. Participants will be asked to rate their perceived overall change in condition of their heel pain from the time that they began the study until the present as ‘worse’, ‘no change’ or ‘better’ [33]. If participants indicate ‘worse’, they will then be asked *how much worse* on a 5-point scale from ‘very much worse’ to ‘slightly worse’. Similarly, if participants indicate ‘better’, they will then be asked *how much better* on a 5-point scale of ‘slightly better’ to ‘very much better’ (Fig. 2). The minimal clinical important change is 2-points [33].

**Fig. 2 Fig2:**
[figure not shown]
Global Rating of Change Score

5.*Physical activity:* Physical activity level will be evaluated using the Active Australia Survey, which is a short and reliable set of questions designed to measure participation in leisure-time physical activity [34]. The survey has exhibited good reliability with ICCs from 0.71 to 0.86 [34].

Physical measurements will consist of IFM morphology and motor performance, plantar fascia thickness, foot posture and mobility, ankle dorsiflexion range of motion, and toe flexor and plantar-flexor strength.

6.*IFM morphology and composition:* IFM morphology will be measured from high-field MRI and dynamic ultrasound images of the foot, respectively. MRI will permit the evaluation of volume and composition (fat infiltration) of the IFMs. The ability to evaluate whole muscle volumes from MRI will provide quantification of non-uniform changes within a muscle. Although measurements of IFM morphology obtained from ultrasound imaging will be limited to discrete measures of cross-sectional area or thickness, it is included as it is a more accessible, less expensive, clinically feasible measure of IFM morphology than MRI. Inclusion of both imaging modalities will provide insight as to whether the clinically feasible technique of ultrasound imaging has sufficient sensitivity to provide similar information regarding IFM morphology as the gold standard MRI.

A high-resolution fat/water separation imaging sequence (3D; TR 8.68 ms; TE 3.06 and 5.61 ms; 3°; FOV 111 × 223 mm; 0.35 × 0.35 × 0.35 mm; contiguous slices; 434 Hz/Px; TA 11 min 12 s) of the entire foot will be acquired using a whole-body 7 Tesla MRI scanner (Magnetom Terra, Siemens, Erlangen, Germany). Participants will be positioned prone with the ankle in plantarflexion to enable the foot to be positioned within the receiver coil (1Tx 28Rx Knee Coil). For individual IFMs (abductor hallucis, adductor hallucis, flexor digitorum brevis, quadratus plantae, abductor digiti minimi, flexor hallucis brevis, flexor digiti minimi, lumbricals and plantar and dorsal interossei), muscle volume and percentage muscle fat infiltration will be measured from the fat-water images. Regions of interest will be manually contoured for each muscle. Muscle volumes and the percentage of muscle fat infiltration (muscle fat infiltration % = Fat/(Fat+Water)*100) will be calculated from the segmented images for each muscle using established methods [35, 36].

A LOGIQ V2 ultrasound machine (GE Healthcare, Illinois, USA) equipped with a linear array probe (6-12 MHz) will be used to obtain images of the IFMs. Cross-sectional area of the abductor hallucis and thickness of the muscles of the first interstitial space (adductor hallucis, first dorsal interossei and first lumbrical) will be imaged in sitting and standing positions using previously established methods [37]. For abductor hallucis, cross-sectional area will be measured from transverse images obtained on a scanning line drawn in an inferior direction from the most anterior aspect of the medial malleolus. Thickness of the muscles of the first interstitial space will be measured from longitudinal images obtained on a scanning line between the first and second metatarsal bones. Cross-sectional area of flexor digitorum brevis, quadratus plantae and flexor hallucis brevis will be measured from transverse images obtained with the participant in prone with the foot relaxed over the edge of the bed [38]. The thickest portion of the flexor digitorum brevis and quadratus plantae muscles will be located in longitudinal along a scanning line from the medial tubercle of the calcaneus to the third toe, and then the probe rotated to 90 degrees to measure the cross-sectional area. For flexor hallucis brevis the thickest portion of the muscle will be located in longitudinal along the first metatarsal shaft and then the probe rotated to 90 degrees to measure the cross-sectional area. For reproducibility at follow-up, the location of the probe will be recorded as the linear distance from the posterior aspect of the calcaneus. Ultrasound images will be stored and measured offline using medical imaging software (Osirix MD, Pixmeo SARL, Geneva, Switzerland). Test-retest reliability of these measures is high with ICCs 0.81 to 0.98, standard error of measurement (SEM) 0.13 to 0.17cm for thickness and 0.13 to 0.19cm^2^ for cross-sectional area, and minimal detectable change (MDC) of 0.36 to 0.48cm for thickness and 0.14 to 0.53cm^2^ for cross-sectional area [37, 38].

7.*Plantar fascia thickness:* Ultrasound imaging will also be used to assess sagittal thickness of the plantar fascia at the anterior margin of the calcaneus, using previously established methods [39]. Participants will be positioned in prone with the foot relaxed over the edge of the plinth and metatarsophalangeal joints relaxed [40]. Longitudinal images will be obtained 0.5 cm medial to the midline of the plantar aspect of the foot [39]. Test-retest reliability has been established with ICC 0.67 to 0.77 [39]. Based on data provided, SMD is estimated as 0.17 to 0.20 mm, and MDC 0.47 mm to 0.55 mm [39].

8.*IFM motor performance:* Motor performance of four foot movements will be rated by an experienced physiotherapist from video recordings. The foot movements will include (1) great toe extension, (2) lesser toe extension, (3) toe spread, and (4) doming. Each movement will be rated on a scale of 0 to 3 (0 = does not initiate movement or starting position cannot be maintained, 1 = partially completes the exercise, 2 = completes the exercise with compensatory movements, slowness or obvious clumsiness and 3 = completes the exercise with a standard pattern) [41]. Examples of compensatory movements include excessive extrinsic muscle contribution (e.g. able to maintain extension of the interphalangeal joints of the toes), movement out of the intended plane of action or unintended overflow into adjacent planes or joints, such as, pronation or supination of the foot and ankle. Fair to substantial test-retest reliability has been reported (ICCs 0.24 to 0.68) [41]. Following each movement task, perceived difficulty will be assessed by asking the participant to rate the task using a 5-point Likert scale (1 = very easy, 2 = somewhat easy, 3 = neutral, 4 = somewhat difficult and 5 = very difficult) [41]. Slight to substantial test-retest reliability has been reported with ICCs 0.15 to 0.96, SEM 0.4 to 0.7 and MDC of 1.1 to 2.0 [41].
9.*Foot posture:* The Foot Posture Index is an established method of visually classifying static foot posture (normal/pronated/supinated) and is calculated from six criterion- based observations [42]. High test-retest reliability has been previously reported with ICC of 0.98 [43]. SEM is estimated as 0.66 and MDC as 1.83, based on data provided [43].
10.*Foot mobility:* Measures of dorsal arch height and midfoot width will be measured with the participant in standing (weight bearing) and sitting (non-weight bearing), using established methods [44]. The difference between weight bearing and non-weight bearing measurements of midfoot height and midfoot width will be calculated to provide an indication of sagittal plane and frontal plane foot mobility, respectively [44]. In addition, foot mobility magnitude will be calculated from these measures to provide a composite indication of foot mobility. Test-retest reliability is high with ICCs 0.60 to 0.98, SEM 0.06 to 0.13 cm, and MDC 0.16 to 0.35 cm [44].11.*Ankle dorsiflexion range of motion:* Weight-bearing ankle dorsiflexion range of motion will be measured using a previously established custom device that is based on the standing lunge test [45]. Participants will stand on the device with their second toe, midpoint of the heel and patella of their test leg aligned perpendicular to a movable upright. While maintaining their heel on the floor, participants will be asked to lunge forward at the ankle, moving the upright forward in the sagittal plane. The examiner will monitor the heel during the movement, ensuring that the heel maintains contact with the ground. At the point where the heel just starts to lift, the examiner will stop the movement and record the horizontal distance between the patella and end of the longest toe (millimetres), indicated by the sagittal displacement of the upright. The test will be repeated three times on each limb, with the average of three measures used in analyses. Test-retest reliability is high (ICC 0.99) and the SEM is 1 mm (MDC estimated as 2.8 mm based on data provided) [45].
12.*Toe flexor and plantar flexor strength:* Strength of the great toe flexors and lesser toe flexors will be assessed using a hand held dynamometer (Lafayette Manual Muscle Tester, Lafayette Instrument Co, Indiana, USA). Participants will be seated with their hips and knees in 90 degrees of flexion, ankle joint neutral and metatarsophalangeal joint at the edge of a step so that the toes can be flexed at the metatarsophalangeal joint [46, 47]. For each test the handheld dynamometer will be placed under the proximal phalanx of the great or lesser toes and stabilized/fixed inferiorly (against ground). To bias intrinsic muscle contribution and minimize extrinsic muscle contribution, participants will be instructed to keep their toes straight at the interphalangeal joints. Participant will be instructed to “push the [great or lesser] toe/s into the dynamometer as hard as you can” to achieve a maximum isometric contraction. Each test will be performed three times with the maximum result being selected for data analysis. Data will be normalized to body weight. Following a period of rest, the tests will be repeated with the participant in standing, with the metatarsophalangeal joint at the edge of a step so that the toes can be flexed. Test-retest of toe flexor strength using a hand-held dynamometer is good with ICCs exceeding 0.67 to 0.92, SEM of 18 N and MDC of 49.8 N [41, 48].

Plantar flexor strength will be measured using the Standing Heel Rise Test [49]. Participants will be asked to “lift the heel as high as possible for each heel rise, until no further repetitions can be performed, keeping the knee and trunk straight”. The test will be performed on a level surface, with the participant barefoot, standing on the test limb, with fingertip support on an adjacent wall to assist balance. Speed of the test will be controlled with a metronome at 60 beats per minute. The test will be stopped when the participant: (i) can no longer complete a full range of heel lift; (ii) cannot maintain pace, or knee and trunk alignment or (iii) uses the wall for assistance rather than balance support. The number of heel rises completed will be recorded. Test-retest reliability is excellent (ICC 0.96, SEM 2.2 repetitions, MDC estimated as 6.1 repetitions from data provided) [49].

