### Interventions

#### Foot exercise plus education

Participants allocated to this group will attend eight individual physiotherapy sessions (weeks 1,2,3,4,5,6,8 and 10) during the 12-week intervention period. Physiotherapy sessions will be 30 min duration and will include detailed education relating to the condition and self-management strategies, as well as an exercise program that will be performed both at home and supervised by the physiotherapist during sessions. Participants will be asked to complete a daily logbook (Additional file 3) of exercises that are completed, symptoms, any physical activity that is undertaken, adverse responses and details of any treatments they have outside of the study protocol.

The 12-week foot muscle focussed training programme will consist of two components: exercises performed daily and exercises performed three times a week. Table 1 provides an overview of the exercise programme and Additional file 4 provides the detailed exercise protocol, including specific instructions for each exercise. Daily exercises will consist of four foot and toe movements and two weight bearing exercises. Exercises performed three times a week will consist of four exercises, each with three stages of progression. Progression is provided by varying the number of repetitions and sets, amount of load and rate of loading. Participants will progress through the stages 1 to 3 in an individualized, criterion-based manner. When the indicated repetitions and sets are reached for a stage, progression is made provided that:
(i)the therapist considers that the patient can adequately recruit the IFMs without excessive extrinsic foot muscle contribution (e.g. able to maintain extension of the interphalangeal joints of the toes) or perform local joint motion at the foot and ankle with optimal control (i.e. smooth motion through the intended plane of action without unintended overflow into adjacent planes or joints, such as, pronation or supination of the foot and ankle);(ii)the participant’s rating of effort of each exercise using Modified Borg Scale is 0–5/10;(iii)the participant’s pain response to loading is adequate (pain during exercise < 5/10 on a numerical rating scale and no change in first step pain the following day).

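### The scoring definition for intrinsic foot muscle motor performance gives an inverted example of a compensatory movement: maintained toe-joint extension is listed as a fault

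*Protocol article*

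**What the plan says.** Item 8 under Secondary outcome measures (IFM motor performance) has four movements: great toe extension, lesser toe extension, toe spread and doming. Each is "rated by an experienced physiotherapist from video recordings". The top two grades are "2 = completes the exercise with compensatory movements, slowness or obvious clumsiness and 3 = completes the exercise with a standard pattern". The text then illustrates compensation: "Examples of compensatory movements include excessive extrinsic muscle contribution (e.g. able to maintain extension of the interphalangeal joints of the toes". Its other illustrations are movement outside the intended plane and overflow into neighbouring planes or joints.

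Two other places in the article use the same physical sign:

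- Interventions, Foot exercise plus education, progression criterion (i): the therapist must judge that the patient can recruit the intrinsic muscles "without excessive extrinsic foot muscle contribution (e.g. able to maintain extension of the interphalangeal joints of the toes".
- Secondary outcome measures, item 12 (Toe flexor and plantar flexor strength): "To bias intrinsic muscle contribution and minimize extrinsic muscle contribution, participants will be instructed to keep their toes straight at the interphalangeal joints".

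**The concern.** The same bracketed example appears in two sentences that describe opposite states. In the progression criterion it illustrates the absence of excessive extrinsic contribution. In item 8 it illustrates its presence. Only one can be meant, and the strength test agrees with the progression criterion.

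The sentence in item 8 is part of the operational definition of an outcome, because compensation is what separates a 2 from a 3. A rater who followed it to the letter would treat correct performance as a fault and would find the actual fault missing from the list. The protocol says that the response profile of the secondary measures will guide decisions in future trials, so an error in how a measure is scored could be carried forward. Others may also take the scoring text from the published article.

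**Working it through.** No formula applies and the plan states no figure to reproduce. The check sets the three places side by side.

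| Place | State described | Role given to straight interphalangeal joints |
|---|---|---|
| Foot exercise plus education, criterion (i) | intrinsic recruitment **without** excessive extrinsic contribution | sign of the desired state |
| Item 12, toe flexor strength | extrinsic contribution minimised | means of reaching the desired state |
| Item 8, motor performance | **excessive** extrinsic contribution, a compensation | sign of the fault |

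**Step 1: is there a reading that makes all three agree?** Taken alone, the bracket in criterion (i) could grammatically attach to the excessive extrinsic contribution itself, which would bring it into line with item 8. But that criterion sets out what the patient must be able to do in order to progress, and the bracket names an ability. It reads naturally as an example of meeting the criterion. Item 12 settles the matter: straight toes are requested there in order to reduce extrinsic contribution. No reading of item 8 as printed is consistent with item 12.

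**Step 2: which place is out of line?** Item 8 is, by two to one. Its bracket matches that in criterion (i) word for word. The likely explanation is that the bracket was carried over from a sentence containing *without* into one that does not, and was not negated.

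**Step 3: what follows from a literal application?**

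- Movement completed, extension maintained, nothing else wrong: it meets a listed example of compensation, so it scores 2. Under the meaning used elsewhere in the article it would score 3. Difference: 3 − 2 = 1 point per affected movement, one third of the scale's range of 3.
- Movement completed, extension lost: this is not among the listed examples. The list is illustrative, so a rater could still mark it down under the general category of excessive extrinsic contribution, but the text does not prompt it.

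**Step 4: how much material could be affected?** At most 20 participants × 2 time-points = 40 video sets, or 40 × 4 movements = 160 ratings. This is a ceiling. It assumes that every participant is filmed at both visits and that the example bears on all four movements, which the protocol does not say.

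**The case against.** The strongest reply is that this is one bracketed example, very probably a copying slip, and that the rest of the definition is sound. The 0 to 3 anchors are coherent, the named category (excessive extrinsic contribution) is right, and the other examples are right. The rater is an experienced physiotherapist. For great toe and lesser toe extension, where extending the toes is the task, penalising extension would be close to absurd and should alert any rater. The last follow-up measurement was on 31 January 2020 and the article appeared on 8 May 2020, so nothing shows that this printed sentence was the rater's working instruction. All of this stands. It limits the likely harm but leaves the printed definition wrong.

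A reader might infer more than the documents support:

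- **That participants were in fact marked down.** This would need the rater to have used the literal wording. The rater's guide is not shown.
- **That up to 4 points could be lost per participant.** The protocol rates each movement separately and defines no total. A loss on all four would also require the two toe-extension tasks to be penalised for extending.
- **That the error biases the comparison against the exercise arm.** Criterion (i) gives interphalangeal extension only as an example within one of two alternatives, the other being controlled local joint motion. How often extension is maintained in each arm, at baseline or at 12 weeks, is not given. A differential effect is conceivable under literal scoring, but it is not shown.
- **That this is the outcome closest to the proposed mechanism.** The Background rests on muscle atrophy and on hypertrophy and strength gains. Muscle morphology and toe flexor strength are at least as close, and neither is touched.
- **That the modest reported reliability (ICC 0.24 to 0.68) makes matters worse.** That figure belongs to the published scale and is unrelated to the inverted example.

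**Conclusion.** The point holds as a wording error in an outcome definition. The example in item 8 contradicts two other places in the same article and is inverted in the current text. Its possible size is one point per affected movement on a 0 to 3 scale, conditional on a rater having applied the sentence literally. Whether that happened is unknown.

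The correction is minor. Motor performance is one of many exploratory secondary measures in a 20-participant feasibility study. The primary outcomes are feasibility, credibility and acceptability, summarised descriptively. The sample size was set by the exploratory purpose, the use of MRI and the funding. Point estimates from this study will feed the sample-size calculation for the full trial, but nothing says that motor performance will drive it.

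The conclusion rests on one assumption: that the progression criterion and the strength test express the intended meaning. Item 12 supports this directly.

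**What to change.** 1. In item 8, change *able* to *unable* in the bracketed example, so that loss of interphalangeal extension becomes the listed sign of excessive extrinsic contribution. The progression criterion and the strength-test instruction need no change for this purpose.
2. Confirm the wording in the rater's guide and how the rater applied it. If the intended meaning was used, record that and stop.
3. Only if the literal wording was used, re-score the affected recordings before analysis, masked to arm. Masked outcome assessment is already planned under Outcome measures.

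The cost is one word and one enquiry. In the worst case it adds re-rating of up to 40 short video sets, provided the recordings were kept, with no further contact with participants. If re-rating were needed and recordings were missing, the report should say which wording governed the scores.
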